### Inclusion and exclusion criteria

In order to be eligible for the study, subjects have to meet five inclusion criteria. First, the minimum age of subjects is set at 18 years. Second, subjects need to experience mild to moderate suicidal thoughts. This is defined as a score between 1 and 26 on the Beck Scale for Suicide Ideation (BSS) [30]. Subjects with no suicidal thoughts (BSS = 0) are excluded as they can not benefit from this intervention. Subjects with severe suicidal thoughts (BSS ≥ 27) are excluded because they need more extensive care. Third, subjects should not be severely depressed. A severe depression is defined as a score ≥ 40 on the Beck Depression Inventory (BDI) [31]. Severely depressed subjects are excluded because they need more extensive care and may not be focused enough to finish the intervention. Both severely suicidal and severely depressed subjects are advised to seek help elsewhere. Fourth, subjects need to have sufficient command of the Dutch language. Finally, subjects need to have access to internet and an e-mail address.

### Inclusion procedure

In order to reduce attrition, a multi-staged inclusion procedure will be used to filter out impulsive applicants who are likely to drop out. Subjects will be recruited through advertisements in newspapers and via banners on the internet. Through these banners, subjects will be directed to a website where a brief description of the study will be provided. On this website, subjects will also be able to register for the study. To register, subjects are required to fill out their age, the BDI, and the BSS, which will serve to screen for severe depression and suicide risk. Subjects under 18 will receive an automated response that they are too young to participate. Subjects who are severely depressed (BDI ≥ 40) and/or at high risk for suicide (BSS ≥ 27), will receive an automated response which explains that participation is precluded. In addition, the urgent advice to seek help is given, which will be facilitated by providing names and websites of relevant organisations in the Netherlands. An automated response is chosen since subjects have not yet provided us with contact information and informed consent. The BSS also serves to detect absence of suicidal thoughts (BSS < 1). In this case, an automated response explaining that participation is not possible is generated. In this response, subjects are advised to visit the GP since applying for this course might indicate that the subject has other (mental health) problems.

When eligible for participation (BSS < 27 and BDI < 40), subjects are required to fill out an e-mail address. They subsequently will receive an e-mail that contains an information brochure, an informed consent form and a link to the baseline questionnaire. On the consent form, subjects have to fill in their contact information, as well as contact information of their GP. This information will only be used if necessary (see 'safety of subjects'). After giving informed consent and filling in the baseline questionnaire, subjects will be included and randomized.

In addition to filling out an e-mail address, eligible subjects are asked to (voluntarily) fill out additional information on gender, age, educational level, social situation (living alone of together), current use of mental health care, and importance to remain anonymous. This information will be used to compare subjects who are included with those that eventually decline participation. It is expected that a substantial number of potential subjects will decline participation because the intervention is offered in a research context in which it is not possible to remain anonymous. Individuals who prefer to remain anonymous, the potential target population, may differ from persons who participate in the study. By obtaining additional data, differences may be identified. On the website, it will be explained why this information is requested and how it will be processed.

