**Methods/Design:**

In this study, a recently developed self-help intervention will be evaluated in a Randomized Controlled Trial. The intervention is based on Cognitive Behavioural Therapy and is aimed at subjects who experience mild to moderate suicidal thoughts. This is defined as a score between 1 and 26 on the Beck Scale for Suicidal Ideation (BSS). Higher and lower scores are excluded. In addition, severely depressed subjects are excluded. In total, 260 subjects will be randomly allocated to the intervention-condition (N = 130) or to the information-control condition (N = 130). Self-report questionnaires will be filled out at baseline, 6 weeks after baseline and 18 weeks after baseline. Primary outcome measure is the reduction in frequency and intensity of suicidal thoughts. Secondary outcome measures are the reduction of hopelessness, anxiety and depression, sleeplessness, worry and quality of life measures.

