### Sample size

The sample size of this study is based on the expected effect on the primary outcome measure, i.e. the reduction in frequency and intensity of suicidal thoughts. In order to be able to demonstrate a clinically relevant effect-size of 0.35 with α = 0.05 and β = 0.80, 100 subjects are needed in each condition. When including an expected drop-out of 30%, the total sample size is determined at 260. The effect-size of 0.35 is based on effect-sizes found in other studies into internet interventions, mainly for depression [28,29].

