##### Suicidal thoughts

The *Beck Scale for Suicide Ideation*, *self report *(BSS) [42] is a 21-item instrument to detect and measure the severity of suicide ideation. The BSS parallels the *Scale for Suicide Ideation *(SSI), which is a semi-structured interview [43]. Each item is scored from 0 to 2. The first five items of the BSS serve to screen for suicide ideation. If the subject selects zero for both item 4 and 5, he or she is instructed to go to item 20. Otherwise, all items are filled out. The last two items (20 and 21) assess the number of suicide attempts and the intent to die during the last attempt. The total score is obtained by adding the first 19 items, and ranges from 0 to 38. A higher score indicates more severe suicide ideation. The BSS has high internal reliability with Cronbach alpha ranging from 0.87 to 0.97, and moderate test-retest reliability (r = 0.54). The concurrent validity is high with the SSI (0.90 - 0.94), and moderate with the BDI suicide item (0.58 - 0.62).

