### Statistical analyses

To test the hypothesis that the self-help intervention is superior to the control condition, the analysis will be conducted on an Intention to Treat basis following the pertinent BMJ & Consort guidelines. Missing observations at follow up will be imputed by regression imputation or multiple imputations, stratified for predictors of outcome and loss to follow-up. Relative improvements in frequency and intensity of suicidal thoughts in the experimental group in comparison with the control group will be calculated by Cohen's *d*. For this confirmatory analysis the primary outcome measure is used (BSS). To the exploratory analyses of the secondary outcome measures, a Bonferroni correction will be applied to control the overall Type I error rate.

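### The suicidal-ideation score taken at registration has only screening uses stated; entering it beside the baseline score as a covariate could recover a little precision at almost no cost (optional)

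*Protocol article*

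**What the plan says.** **Registration.** Under Inclusion procedure, "subjects are required to fill out their age, the BDI, and the BSS, which will serve to screen for severe depression and suicide risk". The same section adds a second eligibility use: "The BSS also serves to detect absence of suicidal thoughts (BSS < 1". No other use of the registration BSS is stated. The voluntary demographic items requested at the same stage, by contrast, are given an analytic purpose: comparing participants with those who decline.

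**Baseline.** Eligible applicants then receive the consent form and a link to a separate questionnaire: "After giving informed consent and filling in the baseline questionnaire, subjects will be included and randomized". The article does not list what that questionnaire contains. Three places make a second BSS very likely. Design sets an assessment at baseline, Safety of subjects counts a pre-measure among the assessments that the two-weekly checks supplement, and Primary outcome measure defines the outcome as a reduction on the BSS.

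**Instrument.** Under Suicidal thoughts, the BSS is reported to have "moderate test-retest reliability (r = 0.54"; no retest interval is given.

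**Analysis.** Under Statistical analyses, "Relative improvements in frequency and intensity of suicidal thoughts in the experimental group" are compared with those in the control group and expressed as Cohen's d. Imputation is to be stratified for predictors of outcome and of loss to follow-up. No model, covariates or definition of the starting score is given.

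**The concern.** If improvement is a simple difference from one pre-randomisation score, all the error in that score enters the endpoint. With a test-retest correlation of 0.54, that error could be considerable. A second pre-randomisation score on the same scale is probably already available for each randomised subject, and it could explain further outcome variance without any new measurement.

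What is at stake is power. The sample size has little slack: 100 completers per arm are said to be needed, while 30% loss from 130 leaves 91.

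There is also a point of timing. An analysis plan written later can choose covariates, but it cannot recover registration answers that were not kept and linked. Whether they are kept is settled by the inclusion procedure that this article describes.

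**Working it through.** **1. The plan's own figure.** Sample size states "clinically relevant effect-size of 0.35 with α = 0.05 and β = 0.80, 100 subjects are needed in each condition". Reading 0.80 as power, n per arm = 2(z_α + z_power)²/d²:
- one-sided: 2(1.645 + 0.842)²/0.35² = 101, which reproduces the stated 100;
- two-sided: 2(1.960 + 0.842)²/0.35² = 129 after rounding up, which does not.

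The next step is "When including an expected drop-out of 30%, the total sample size is determined at 260". This reproduces as 100 × 1.30 = 130 per arm. Expected completers are 130 × 0.70 = 91 per arm, the figure used below.

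**2. Inputs.** From the article: d = 0.35, α = 0.05, 130 per arm, 30% drop-out.

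Assumed, because the article does not give them:
- a two-sided test;
- equal variances, with d in units of the SD of one BSS score;
- correlation of the baseline score with outcome r2 = 0.54, borrowed from the test-retest figure;
- correlation of the registration score with outcome r1 from 0.30 to 0.54;
- correlation between the two pre-scores q from 0.54 to 0.90.

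**3. Variances, in units of one score's variance.**
- Improvement from one score: 2 − 2·r2 = 2 − 1.08 = 0.92.
- Adjusted for one score: 1 − r2² = 1 − 0.2916 = 0.708.
- Adjusted for both: 1 − (r1² + r2² − 2·r1·r2·q)/(1 − q²). When r1 = r2 = r this reduces to 1 − 2r²/(1 + q).
- Improvement from the mean of two scores: 1 + (1 + q)/2 − (r1 + r2).

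**4. Power.** Noncentral t, 91 per arm, standardised effect 0.35/√variance.

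| Analysis | q | r1 | Variance | Power |
|---|---|---|---|---|
| Improvement, one score | – | – | 0.920 | 69% |
| Adjusted, one score | – | – | 0.708 | 80% |
| Adjusted, both | 0.54 | 0.54 | 0.621 | 85% |
| Adjusted, both | 0.70 | 0.54 | 0.657 | 83% |
| Adjusted, both | 0.80 | 0.54 | 0.676 | 81% |
| Adjusted, both | 0.54 | 0.40 | 0.692 | 81% |
| Adjusted, both | 0.54 | 0.30 | 0.708 | 80% |

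Moving from the improvement score to adjustment for one score cuts the variance by 23% (0.920 to 0.708). Adding the second score cuts what remains by 12% at best in this table (0.708 to 0.621), and by almost nothing when r1 is about 0.30.

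**5. Averaging the two scores instead.**
- Most favourable case tried, q = r1 = r2 = 0.54: 1 + 0.77 − 1.08 = 0.69, power 81%.
- q = 0.80, r1 = r2 = 0.54: 1 + 0.90 − 1.08 = 0.82, power 74%.
- q = 0.80, r1 = 0.40, r2 = 0.54: 1 + 0.90 − 0.94 = 0.96, power 67%, which is worse than the 69% from one score.

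In general the mean is worse than the baseline score alone whenever r2 − r1 exceeds (1 − q)/2. At q = 0.80 and r2 = 0.54 that means r1 below 0.44; at q = 0.54, below 0.31.

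**6. Sensitivity to the borrowed 0.54.** If both pre-scores correlate 0.30 with outcome and 0.54 with each other, the adjusted variance goes from 0.910 to 0.883 (−3%). If both correlate 0.70 with outcome and 0.70 with each other, it goes from 0.510 to 0.424 (−17%).

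**The case against.** **Nothing here is wrong as written.** One pre-randomisation score is a normal choice and leaves the randomised contrast unbiased. Range restriction of the registration score by the entry rule happens before allocation and in both arms alike, so it creates no bias either. This stands, and it limits the point to an optional improvement.

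**The gap is partly silence.** A reader might infer that the plan discards the registration score and analyses a single noisy measurement. The article does not say so. It fixes no baseline definition and no covariates, which a condensed article may leave to an analysis plan not shown, and predictors of outcome in the imputation could already include this score. Likewise, that every randomised subject completes the BSS twice is a strong inference, not a stated fact. What remains is that the article names only screening uses for the score and does not say it will be kept for analysis.

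**A larger gain is tempting.** A reader might take the rise from 69% to 81% under averaging as the price of the current plan. That needs an unadjusted improvement score, two pre-scores that predict outcome equally well, and a correlation of only 0.54 between them. The registration score is older and range-restricted, so a weaker link with outcome is plausible, and averaging can then reduce power. Averaging also replaces change from the stated baseline assessment with a different endpoint.

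**The 0.54 may not be measurement noise.** Without a retest interval, it may partly reflect real change in ideation. This is a further reason to let a model weight the two scores.

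**Registration answers precede consent.** This is a real cost. It can be met by telling subjects and using the answers only for those who consent.

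**Conclusion.** The point holds as an optional efficiency improvement, not as an error or contradiction in the plan. Against a plain improvement score, a model with both pre-randomisation BSS scores lowers the variance from 0.92 to about 0.62 to 0.71 and raises power from about 69% to about 80% to 85%. Most of that comes from baseline adjustment, which alone reaches about 80%; the registration score itself adds about 0 to 5 percentage points. If the unseen analysis plan already adjusts for baseline, only that smaller increment is at issue.

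The figures rest on an assumed baseline-outcome correlation of 0.54, 91 observed per arm, d = 0.35 in raw SD units and a two-sided 5% test. They also assume that the baseline questionnaire contains the BSS. If it does not, there is no second score to add, and the registration score would have to be the baseline value, which the article should then say.

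**What to change.** - State that the baseline questionnaire includes the BSS and that this score is the baseline value.
- Keep the registration BSS and BDI for consenting subjects and link them to the trial record, for instance through the e-mail address given after screening. Add one line to the information brochure saying so.
- Estimate the primary between-arm BSS difference in a model with the baseline-questionnaire BSS and the registration BSS as two separate covariates. Do not average them into the improvement score.
- Compute Cohen's d by dividing the adjusted difference by the SD of the baseline-questionnaire BSS, so that it stays on a raw-score scale for comparison with the planned 0.35.
- Name the registration BSS and BDI among the predictors in the imputation model.

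Cost: analysis wording, one brochure line (with whatever notice to the ethics committee that entails), one more variable to link and about one degree of freedom. No new measurements or subjects are needed.

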### Randomization

Subjects will be randomized in blocks of 20 after stratification for gender. An independent researcher makes the allocation schedule using random allocation software. Subjects will be informed about the randomization outcome by means of an e-mail, which will also contain a login code for the assigned condition.

### Safety of subjects

Since this study will be conducted in a vulnerable population in which suicide may occur, a safety protocol has been developed. In addition to the pre-, post and follow-up measures, suicidal thoughts will be assessed bi-weekly in both the experimental and the control condition during the first six weeks by means of the BSS and the BDI. The safety protocol will be applied when a subject exceeds the determined cut-off scores, i.e. BSS ≥ 27 or BDI ≥ 40. When this occurs, the researchers will contact the subject by phone on the same day the score is received to assess the suicide risk and contact the GP if necessary. If the phone is not answered, calling will be continued for two days on different times of the day. In case of no response after two days, a standardized e-mail expressing worry will be sent. In this e-mail, it will also be requested to contact the researchers. In addition, it will be explained that the GP will be contacted three days after sending this e-mail. If the GP is not reached, the locum GP is contacted. In case a subject drops out of the study, i.e. does not fill in the questionnaires, an e-mail will be sent with the request to reply and the explanation that the GP will be contacted in case of no reply within three days.

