## Methods/Design

### Design

This study is a randomized controlled trial comparing a web-based self-help intervention with a waitlist control condition. The intervention is aimed at persons with mild to moderate suicidal thoughts. Subjects in the control condition will have access to an information website and will start the intervention after the experimental group has finished (i.e. after six weeks). Assessments will take place at baseline, 6 weeks after baseline and 18 weeks after baseline.

This study was approved by the Medical Ethics Committee of the VU University Medical Centre (registration number 2008/204).

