#### Structure

The intervention consists of six modules, each of which can be completed in one week. A module starts by providing information, followed by an assignment and several exercises. Subjects are strongly advised to complete those. In addition, each module contains a number of optional exercises from which the subject can choose the ones that appeal to him. Finally, each module is provided with a number of 'Frequently Asked Questions'. Here, subjects can also actively pose questions which will be answered on a general, non personal level. Consequently no personal feedback or support by a therapist will be offered.

Ideally subjects need to spend at least 15 minutes twice a day to perform the exercises. Every week, an automated e-mail is sent as a reminder of the new module and as motivation to complete it.

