#### Waiting list control condition

Subjects in the control condition can access a website where information on suicidality is provided. The information is meant to inform them about the nature and possible causes of their thoughts and feelings. Discussed themes are prevalence, risk factors and warning signs. Also, information about treatment in general is provided, as well as links to several mental health organisations. After six weeks, subjects are provided with a login code for the intervention.

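### Fortnightly safety scores stop at week 6, when control subjects first receive the unguided intervention; their next scheduled score is at week 18

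*Protocol article*

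**What the plan says.** All references are to the protocol article.

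- **Monitoring.** Under Safety of subjects, "suicidal thoughts will be assessed bi-weekly in both the experimental and the control condition during the first six weeks", with the BSS and BDI, on top of the baseline, post and follow-up measures. A BSS of 27 or more, or a BDI of 40 or more, leads to a telephone call the same day and contact with the GP if needed. There is a second trigger: "In case a subject drops out of the study, i.e. does not fill in the questionnaires, an e-mail will be sent", followed by contact with the GP if there is no reply within three days.
- **Measurement schedule.** Under Design: "Assessments will take place at baseline, 6 weeks after baseline and 18 weeks after baseline".
- **Control access.** Under Design, controls begin the intervention once the experimental group's six weeks are over. Under Waiting list control condition: "After six weeks, subjects are provided with a login code for the intervention".
- **The programme.** Under Structure: "The intervention consists of six modules, each of which can be completed in one week", and "Every week, an automated e-mail is sent as a reminder of the new module and as motivation to complete it". On guidance: "Consequently no personal feedback or support by a therapist will be offered".

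**The concern.** The article gives the risk of suicide in this population as its reason for having a safety protocol. The Discussion adds that anonymous participation was ruled out so that the researchers could follow subjects and intervene. Yet the fortnightly checks end at about the moment controls are given a new, unguided programme. Experimental subjects are scored every two weeks while they work through the same programme, and the article gives no reason for treating controls differently during theirs.

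What is at stake is subject safety. A control who worsens after receiving access would be picked up by the schedule only at week 18. The point does not depend on the intervention being harmful, and it has no bearing on the randomised comparison at week 6.

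**Working it through.** The plan gives no figure to reproduce here. The check is a timeline built from the stated schedule.

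**Inputs**

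- Fortnightly BSS/BDI in both arms, first six weeks only (Safety of subjects). Bi-weekly is read as every two weeks, which is an assumption. If it meant twice a week, the contrast below would be larger.
- Main measurements at weeks 0, 6 and 18 (Design).
- Controls start after week 6 (Design; Waiting list control condition).
- Six modules at one per week, so a six-week course (Structure).
- 130 subjects per arm, 260 in total (Abstract).

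**Scheduled scores.** Combining the two schedules gives weeks 0, 2, 4, 6 and 18 in both arms.

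**Longest interval between scheduled scores**

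- Weeks 0 to 6: 2 × 7 = 14 days.
- Weeks 6 to 18: (18 − 6) × 7 = 84 days.
- Ratio: 84 / 14 = 6.

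**Scores during planned use**

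| Arm | Planned use | Scores after access, within planned use | Next score |
|---|---|---|---|
| Experimental | weeks 0 to 6 | weeks 2, 4, 6: three | week 18 |
| Control | weeks 6 to 6 + 6 = 12 | none | week 18 |

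The control window is inferred from the weekly pace; the article does not state it as a schedule for controls. The count of zero depends little on that inference: whatever pace a control follows, nothing is scheduled after access until week 18.

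**Can a trigger arise between weeks 6 and 18?** The cut-off trigger needs a received score, and the drop-out trigger needs a questionnaire left unanswered. With no questionnaire due, neither can newly arise. A high or missing week-6 score would still be followed up, but that reflects the subject's state at about the time of access, not during use.

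**The case against.** The strongest reply is that this is an explicit and symmetric design choice. The article bases monitoring on the population's risk, not on exposure to the intervention, which is why controls are also checked while they have only an information website. On that footing both arms have the same gap from week 6 to week 18, and nothing shows that controls are at higher risk in it than experimental subjects. Controls also reach the programme after more checks than experimental subjects had: screening at registration, scores through week 6, and follow-up of a missed week-6 questionnaire. Their use in weeks 6 to 12 is inferred, no deterioration rate is given, and extra checks in controls alone would make contact unequal before week 18. Finally, the article summarises a safety protocol that is not shown.

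Much of this stands. The schedule does not contradict itself, the gap is shared, expected harm cannot be quantified, and experimental subjects who work slowly may also use the programme unmonitored after week 6. It does not remove the point, however. If the population's risk is the reason for monitoring, that argues for continuing it and does not explain stopping as controls start an intervention the authors describe as the first of its kind. Checks before access cannot detect worsening after it. The six-week limit is stated outright for both conditions, so this is not a detail lost in condensing the article. If the full safety protocol goes further, this sentence needs correcting. The concern about unequal contact bears on which form of the remedy to choose.

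**Conclusion.** The concern holds on the text as written. Both arms go 84 days without a scheduled safety score, but only for controls does that gap cover the whole planned course: none of their scheduled checks falls within it, against three in the experimental arm. Up to 130 people are affected, fewer if some never use the login.

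The figures rest on two assumptions: that bi-weekly means every two weeks, and that controls follow the pace of one module per week. Confidence is moderate, because the full safety protocol is not shown. This is a safety improvement that should be made. It is not an error that undermines the trial.

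**What to change.** Amend Safety of subjects so that the BSS/BDI checks, with the same cut-offs and the same telephone, e-mail and GP procedure, also take place at weeks 8, 10 and 12. At the planned pace, the longest interval between scores during control use then falls from 84 to 14 days.

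- **Controls only:** at most 3 × 130 = 390 extra online assessments. The drawback is more assessment and researcher contact for controls than for the experimental arm before the week-18 measure.
- **Both arms:** at most 3 × 260 = 780. This keeps contact equal up to week 18 and also covers experimental subjects still working through the modules.

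Either option adds some calls and possible GP contacts. No new instrument or contact information is needed, since subjects already give their own and their GP's details on the consent form (Inclusion procedure). The week-6 comparison is unchanged either way. If the full safety protocol already extends the checks, it is enough to correct the sentence.
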